**Fig. 2 Fig2:**
[figure not shown]
Key timepoints for assessing outcomes of exercise prehabilitation intervention

### Primary outcome

#### Cardiopulmonary fitness

Cardiopulmonary fitness will be determined, by a maximal cardiopulmonary exercise test (CPET), the gold standard measure of fitness [23]. Cardiopulmonary exercise tests will be performed in the CRF at St James’s Hospital under medical supervision at Dx (oesophageal cancers only), T0 and T1. The CRF at St James’s is equipped with an electromagnetically braked cycle ergometer (COSMED, **E200 P/K)**, COSMED K4b2 ambulatory metabolic system, integrated exercise ECG and integrated blood pressure monitoring. The CPET will be performed using a ramp cycle ergometer protocol. Following a standardised resting and warm-up period, testing will commence with 3 minutes of free-wheel pedalling after which resistance will increase by standardised increments. The ramp gradient will be set to 10–25 W/min based on the equation below by Wasserman et al. [24].
i.VO_2_unloaded in ml/min = 150 + (6 x weight kg)ii.Peak VO_2_in ml/min = (height cm – age years) × 20 (sedentary men) × 14 for sedentary womeniii.Work rate increment minute/watts = (peak VO_2_ml/min – VO_2_unloaded ml/min)/100)

Breath-by-breath gas analysis, heart rate, heart rhythm (12-lead ECG), non-invasive blood pressure, oxygen saturation, rate of perceived exertion and blood lactate will be measured before, during and after testing. The test will be terminated by a cool-down performed at a resistance of 30 watts for 3 minutes and during which participants will be monitored for signs of distress (pallor, chest pain, dyspnoea). VO_2_peak will be calculated as an average over the last 30 seconds of exercise. AT will be described as lactate threshold (LT) and ventilatory threshold (VT). Lactate Threshold (LT) will be measured via ‘a pin-prick’ blood sample, analysed using the ‘Stat Strip Xpress LAC’ portable lactate monitor. Samples will be collected and recorded every minute during the exercise test. Post completion of the test, the results will be inputted on a graph against time/work rate. The LT is the point in which VO_2_ increases non-linearly, this will be calculated via visual inspection, a valid method of determining LT. VT will be determined through the modified v-slope method, which determines the point of the change in slope of the relationship of VO_2_above which VCO_2_ increases faster than VO_2_ without hyperinflation [19]. Other components of fitness that will be obtained from breath-by-breath analysis include: VE/VCO_2_, VE/ VO_2_, minute ventilation.

### Secondary outcomes

#### Secondary outcome 1: postoperative morbidity

Postoperative morbidity will be measured using a suite of validated instruments; the Clavien-Dindo Scale, the postoperative morbidity index (POMS) and the Comprehensive Complications Index (CCI)**.** These widely used objective measures of postoperative complications, overcome the known issues with standardising the definition of postoperative complications [4]. In addition, hospital and critical care LOS and postoperative mortality will be recorded. All outcomes will be recorded on hospital discharge and on POD30 with the exception of the POMS which will additionally be recorded on POD3, POD5 and POD7 (Table 1).

##### Clavien-Dindo scale

The Clavien-Dindo classification score measures the most severe complication that occurs in the postoperative period. The ordinal scale is divided into seven grades (Grade I-V, two sub-groups each for Grade III and IV), ranging from Grade I, which considers any deviation from normal, to Grade V, which describes death of the patient. The tool is widely used due to its simplicity and reproducibility, its correlation with LOS, and the degrees of severity of complications also correlate with the perceptions of severity of medical staff and patients [25].

##### The post-operative morbidity score (POMS)

The POMS is a nine-domain tool that prospectively describes and records in-hospital postoperative complications following major surgery [26]. The POMS, which is performed on specific postoperative days, typically POD3, POD5 and/or POD7, provides defined criteria for complications in nine categories classified by organ system including pulmonary, infectious, renal, gastrointestinal, cardiovascular, neurological, haematological, wound and pain.

##### The comprehensive classification index (CCI)

The CCI provides a summary of overall morbidity including the type, number and severity of each complication experienced during the postoperative period [25]. When compared to the Clavien-Dindo Classification the CCI demonstrates a superior ability to discriminate between patients with a different number and severity of complications.

### Secondary outcome 2: pulmonary and physical performance

The training stimulus associated with HIIT may lead to important improvements in secondary measures of physical performance including pulmonary function, ventilatory and peripheral muscle strength and functional capacity [27], which may in turn positively impact postoperative outcome. The following measures will be performed at Dx, T0 and T1. Self-reported functional recovery will be evaluated on POD30.

#### Pulmonary function

Pulmonary function will be measured as the first step of the CPET and analysed as a secondary outcome. The COSMED K4b2 ambulatory metabolic system will be used to determine forced vital capacity (FVC), forced expiratory volume at 1 s (FEV1) and the ratio of FEV1/FVC in accordance with the American Thoracic Society Guidelines.

#### Maximal inspiratory pressure

Maximal inspiratory pressure (PImax) provides a non-invasive, simple measure of inspiratory muscle strength, particularly the diaphragm. PImax will measured using a PowerBreathe K-series portable respiratory pressure metre. Patients will be measured at residual volume during a forceful inspiratory manoeuvre while resting in a seated position. All measures will be performed in triplicate with the best measure taken for data entry.

#### Peripheral muscle strength

Preliminary analysis of the PHIIT trial participants has demonstrated a post-intervention increase in peak power output, suggesting some improvement in lower limb strength with the cycle ergometer HIIT protocol. In the proposed study, quadriceps muscle strength will be measured by 1 repetition maximum (1RM) using a horizontal leg extension. The 1RM is defined as the highest load that can be lifted through full range of movement at one time. Participants will complete 1RM testing following adequate aerobic warm up followed by a warm up of 6 repetitions at 60% 1RM with 2 min rest and then 3 repetitions at 80% 1RM with 2 min rest. A maximum of 5 trials to determine 1RM will be completed with a rest period of 2 minutes between each trial.

#### Functional performance

This will be measured using the Short Physical Performance Battery (SPPB). This measure combines the results of gait speed, chair stand and balance tests. A score lower than 10 indicates one or more mobility limitations.

#### Self-reported physical activity

Physical activity will be measured subjectively using the self-administered International Physical Activity Questionnaire (IPAQ). The IPAQ long form comprises four activity domains (work, leisure, transportation and household) which evaluates activity in metabolic equivalent (MET)-hours per week over the previous 7 days. The questionnaire also quantifies average weekend and weekday sitting time. Data collected on POD30 will be collected via a telephone call with the participant.

#### Self-reported functional recovery

Patient perceived physical recovery at POD30 will be self-assessed using standardised classifications. Participants will rate their recovery as 0, 25, 50, 75% or 100% according to standardised descriptors [28]. Data collected on POD30 will be collected via a telephone call with the participant.

### Secondary outcome 3: quality of life

The EORTC QOL questionnaire is an integrated system for assessing the health related QOL of cancer patients participating in international clinical trials. The core questionnaire, the QLQ-C30 has been used in a wide range of cancer clinical trials [29]. It is supplemented by disease specific modules. Categories include functional scales, global health status and QOL scale, in addition to several single-item symptom measures. Disease specific modules such as the oesophageal EORTC QLQ-OES18 and QLQ-OES25 and the lung EORTC QLQ-LC 13 can be used in conjunction with the main questionnaire to monitor disease specific symptoms. In the current study, QOL will be measured using EORTC QLQ-C30 and relevant subsets at Dx, T0, T1 and on POD30.

QOL will be further measured using the EuroQol (EQ) EQ-5D5L to analyse cost effectiveness of the intervention. The EQ-5D5L comprises five dimensions: mobility, self-care, usual activities, pain/discomfort and anxiety/depression with each dimension rating activities as having no problems, having slight problems, having moderate problems, having severe problems and being unable to do/having extreme problems. The EQ-5D5L will be measured at routine post-operative clinic visits at 6 weeks and 3 months postoperatively.

Changes in the QOL scores (both from EORTC QLQ and EQ5D5L) will be analysed to identify any difference in the profile of health related QOL in the two arms of the study. If costs of hospital care are lower in the intervention group, and if QOL scores are better post-intervention, then the intervention will dominate (ie, lower costs of hospital care, including the cost of the exercise programme, and better QOL of patients) and no cost-effectiveness ratios can be calculated. Otherwise it will be possible to estimate the additional cost of any measured improvement in QOL post-intervention. Similarly, if costs of care are lower in the intervention group but QOL is also lower, it will be possible to estimate cost-effectiveness ratios for this change.

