**Secondary outcomes**					
*Pulmonary and Physical Performance*					
Functional performance	Short Physical Performance Battery (SPPB)	X	X	X	
Muscle Strength	Leg Press 1-RM	X	X	X	
Physical activity	International Physical Activity Questionnaire	X	X	X	
Pulmonary Function	CPET	X	X	X	
Maximum Inspiratory Pressure	PowerBreathe K-series	X	X	X	
Nutritional Status	Dietary interview	X	X	X	
Quality of Life	EORTC-QLQ-C30	X	X	X	X
Cancer specific quality of Life	EORTC-QLQ-OG25 (oesophago-gastric cancer)	X	X	X	X
	EORTC-QLQ-LC 13 (lung cancer)	X	X	X	X
Qualitative approach	Semi –structured interviews (focus groups or 1:1)			X	
Cost analyses	EQ5D				X
	Service Use Inventory				X

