### Hospital resources

The costing of hospital stays, and interventions will be carried out based on activity data from hospital records, with unit costs taken from the standard estimated costs from the Healthcare Pricing Office. Programme implementation costs will be analysed in consideration of clinician salaries, overheads and equipment costs. Formal care costs will be extracted from medical charts and from the institutional database in consideration of preoperative characteristics, surgery type and postoperative recovery including complications. Since the participants in the study are randomised to each arm, the comparison of costs of hospital stays will be reported as differences and the normal tests of significance. It is also important to assess if the intervention has longer term effects beyond hospital discharge. The destination at discharge, use of community health services from the time of discharge to the follow up outpatient appointment and EQ5D5L scores at the time of the follow up appointment will be collected for each participant. This will allow the measurement of any effects of the intervention on the feasibility of the patient going home directly from hospital, and any difference in the need for community health services. The EQ5D5L scores at outpatient follow up will allow an assessment if any short-term difference persists and will assist in modelling the likely medium-term effect of the intervention on costs and QOL.

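### EQ-5D-5L is first measured six weeks after surgery, so the planned analysis of its changes cannot show change from before the intervention

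*Protocol article*

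**What the plan says.** Under Secondary outcome 3: quality of life, the protocol article gives EQ-5D-5L its purpose: "QOL will be further measured using the EuroQol (EQ) EQ-5D5L to analyse cost effectiveness of the intervention". It then fixes the times: "The EQ-5D5L will be measured at routine post-operative clinic visits at 6 weeks and 3 months postoperatively". Table 1 agrees. EQ5D stands in the "Cost analyses" row, marked in the post-operative column only, with the Dx, T0 and T1 cells empty.

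The EORTC instruments have a different schedule: "QOL will be measured using EORTC QLQ-C30 and relevant subsets at Dx, T0, T1 and on POD30".

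The same section plans one analysis for both instruments: "Changes in the QOL scores (both from EORTC QLQ and EQ5D5L) will be analysed to identify any difference" in the quality-of-life profile of the two arms. It then describes a dominance rule and, failing dominance, a cost per measured improvement in quality of life.

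Hospital resources adds two statements. "EQ5D5L scores at the time of the follow up appointment will be collected for each participant", and "EQ5D5L scores at outpatient follow up will allow an assessment if any short-term difference persists". The Measures section also announces a further quality-of-life assessment three months after the intervention, without naming the instrument.

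**The concern.** One sentence treats EORTC and EQ-5D-5L alike, but only EORTC has a value from before the intervention. A reader who follows the plan would take change to mean change from T0, as it can for EORTC, and would find no T0 score for EQ-5D-5L. The change that can be formed, from 6 weeks to 3 months, describes late recovery and not the effect of the programme.

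EQ-5D-5L is the instrument chosen for cost-effectiveness, and a baseline score not collected before randomisation cannot be recovered afterwards. Without it, the analysis also loses a covariate that would sharpen a comparison between two arms of 39.

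**Working it through.** **Which EQ-5D-5L quantities the stated schedule supports**

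- Change from T0: not computable, because there is no T0 score.
- Change from T0 to T1, the pre-operative effect of the programme: not computable.
- Change from 6 weeks to 3 months after surgery: computable.
- Arm difference at 6 weeks and at 3 months: computable.
- Unadjusted cost-effectiveness ratio from a post-operative arm difference: computable.
- Any utility comparison adjusted for baseline: not computable.

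**Why the available change can mislead**

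Let D6 and D3 be the differences in mean EQ-5D-5L, intervention minus control, at 6 weeks and at 3 months. The arm difference in change is D3 − D6. Suppose the intervention arm is ahead at both visits and the control arm partly catches up, so that D6 > D3 > 0. Then D3 − D6 is negative: the analysis of change points against the intervention although that arm is better at both visits.

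**What a T0 score would add**

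The plan states no figure for EQ-5D-5L. Its one design calculation concerns VO2peak. That figure reproduces (exact t-test power of 80.3% at 32 per arm) and does not bear on this point.

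Inputs:
- n = 39 per arm, from the Abstract (78 in total, 1:1).
- Correlation ρ between T0 and follow-up EQ-5D-5L: not in the documents, assumed 0.3 to 0.7.
- Results are in units of the EQ-5D-5L standard deviation (SD), taken as equal in both arms. The documents give no value for it.

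Formulas:
- SE of the arm difference without baseline = SD × √(2/n)
- SE adjusted for baseline = SD × √(2(1 − ρ²)/n)
- Reduction in variance = ρ²

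Results at n = 39:

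| | SE (in SD) | Variance reduction |
|---|---|---|
| Unadjusted | √(2/39) = 0.226 | none |
| ρ = 0.3 | √(2 × 0.91/39) = 0.216 | 9% |
| ρ = 0.5 | √(2 × 0.75/39) = 0.196 | 25% |
| ρ = 0.7 | √(2 × 0.51/39) = 0.162 | 49% |

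The chance difference between the arms at T0 itself has SE 0.226 SD, a 95% range of about ±1.96 × 0.226 = ±0.44 SD. On average the fraction ρ of it carries through to follow-up. At ρ = 0.5, a one-SE imbalance shifts the follow-up difference by 0.5 × 0.226 = 0.113 SD.

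**Follow-up times side by side**

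- Measures: three months after the intervention.
- Secondary outcome 3: 6 weeks and 3 months after surgery.
- Hospital resources: one outpatient follow-up appointment.

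Surgery follows the intervention, so the first two are not counted from the same date. The third does not say which of the two visits it means.

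**The case against.** The strongest reply is that the plan still works as a randomised comparison. The stated purpose is to find a difference in quality-of-life profile between the arms, and scores at 6 weeks and 3 months give a post-operative profile. Randomisation makes those differences unbiased, and chance imbalance at T0 is already counted in their standard error. EORTC covers the pre-operative and early post-operative period. All of this stands. It limits the loss to precision and to the missing change from baseline, but it does not give the change analysis a starting point.

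Stronger readings are tempting, and the documents do not support them:

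- A reader might infer that no EQ-5D-5L change or cost-effectiveness ratio can be computed. The later change, the arm differences and an unadjusted ratio all can.
- A reader might infer that the persistence statement in Hospital resources is impossible to carry out. It is only unclear. The earlier difference could be in hospital costs, in EORTC scores at T1 or POD30, or in EQ-5D-5L at 6 weeks. The last of these fits poorly with a section that mentions a single appointment.
- A reader might infer that a planned baseline-adjusted economic analysis fails. None is planned. Baseline adjustment is stated only for the primary-outcome model.
- A reader might infer that a stated trial aim is lost. The listed aim concerns healthcare costs, which need no EQ-5D-5L. Cost-effectiveness enters as the purpose of the questionnaire.

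**Conclusion.** The point holds in a limited form. Text and Table 1 agree on a schedule without any EQ-5D-5L score before surgery, so this is a stated design feature and not a detail lost in condensing the article. It conflicts with the planned analysis of changes if change means change from before the intervention. The change that remains starts after both the intervention and the operation.

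The cost in precision is a 9% to 49% reduction in variance forgone, for assumed correlations of 0.3 to 0.7. The documents give neither a correlation nor a utility SD, so the size is illustrative. A reader might treat a chance baseline imbalance as bias that passes in full into the cost-effectiveness ratio. It is not bias under randomisation, and full carry-over would need a correlation of 1.

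Severity is moderate. The primary outcome and the validity of the randomised comparison are unaffected.

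**What to change.** 1. Add EQ-5D-5L at T0 and T1 and mark both in Table 1. T0 precedes randomisation, so its score is a proper covariate. T1 follows randomisation, so its score is an outcome and should not be adjusted for.
2. Compare the arms on post-operative EQ-5D-5L adjusted for the T0 score, in place of an analysis of change from 6 weeks to 3 months.
3. If the form is not added, or recruitment is too far advanced for it, restate the EQ-5D-5L analysis as a comparison of post-operative scores and keep the wording on changes for EORTC only.
4. In Hospital resources, state which measure and which time give the short-term difference whose persistence is to be judged.
5. Reconcile the quality-of-life follow-up times in Measures, Secondary outcome 3 and Hospital resources, and name the instrument for each.

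The cost of items 1 and 2 is a five-item form at two visits where EORTC forms are already completed, plus a protocol amendment. Items 3 to 5 are changes of wording.

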## Background

Cancer prehabilitation is an essential component of the multidisciplinary treatment model that optimises patient outcomes at each step on the continuum of cancer care, from diagnosis to survivorship [1, 2]. Prehabilitation aims to reduce post-treatment morbidity and improve pre-treatment health status to increase treatment options, typically surgical candidacy. With the evolution of multimodal approaches to cancer treatment [3], there are now multiple opportunities for prehabilitation in oncology care.

Attenuating postoperative risk is a key priority of preoperative assessment and enhanced recovery after surgery (ERAS) protocols. In lung and oesophageal cancer, complex surgical resection is the only curative intervention, however these procedures are associated with significant postoperative challenges and have the highest mortality and major morbidity risk compared to other oncologic surgeries. Postoperative pulmonary complications (PPCs), which are among the most serious postoperative morbidity, occur in 15–30% of patients post-oesophagectomy and are the primary cause of postoperative mortality, contributing to 45.5–55% of post-oesophagectomy deaths [4]. Comparably, rates of PPCs following thoracic surgery are 25% [5]. The impact of postoperative complications, particularly PPCs on long-term morbidity and quality of life (QOL) is well documented [6], and leads to significant hospital cost, driven by increased use of critical care facilities, and protracted hospital length of stay (LOS). The median cost of hospitalisation post oesophagectomy is $31,375 (€26,368), however this increases by a further $20,777 (€17,461) with serious postoperative complications [7]. Consequently, interventions aimed at reducing postoperative risk may have significant clinical and economic impact.

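### The economic rule calls the programme dominant on the direction of two differences, with no joint uncertainty attached, and leaves the costlier-and-worse outcome unnamed

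*Protocol article*

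**What the plan says.** The rule is in the protocol article, Secondary outcome 3: quality of life. Its condition is "If costs of hospital care are lower in the intervention group, and if QOL scores are better post-intervention", and its conclusion is "then the intervention will dominate (ie, lower costs of hospital care, including the cost of the exercise programme, and better QOL of patients". In that case the article says no cost-effectiveness ratio can be calculated. Two further sentences cover the other outcomes:

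- The fallback: "Otherwise it will be possible to estimate the additional cost of any measured improvement in QOL post-intervention".
- Cheaper but worse: "if costs of care are lower in the intervention group but QOL is also lower, it will be possible to estimate cost-effectiveness ratios".

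The QOL input is described as follows: "Changes in the QOL scores (both from EORTC QLQ and EQ5D5L) will be analysed to identify any difference". The rule names neither the score nor the time point that decides. EQ-5D-5L is scheduled at 6 weeks and 3 months after surgery, and Table 1 shows it only in the postoperative column.

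Under Hospital resources, "the comparison of costs of hospital stays will be reported as differences and the normal tests of significance". The programme is costed separately: "Programme implementation costs will be analysed in consideration of clinician salaries, overheads and equipment costs". No amount is given.

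**The concern.** Dominance is the strongest claim an economic evaluation can make, because it removes the need to weigh cost against benefit. Here it follows from direction alone. The printed condition can be met by two small chance differences, and nothing in the sentence requires the reader to be told how likely that is. The two differences are probably linked, since complications raise cost and can be expected to lower QOL, and that makes a chance finding of cheaper and better more likely.

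The treatment of outcomes is also lopsided. The favourable corner (cheaper and better) has a name and a conclusion. The opposite corner (costlier and worse, where the programme is dominated) has neither. The effect on hospital costs is a stated secondary aim and features in the abstract and discussion, so an unsupported claim of dominance could be widely quoted.

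**Working it through.** **The plan's own figures.** The economic rule has no stated error rate, power or sample size. The only design calculation is for VO2peak: 32 per arm, difference 1 ml/kg/min, SD 1.4, two-sample t-test. It reproduces (80.3% power) but says nothing about cost or QOL. The abstract gives 39 per arm recruited, which is used below.

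**Step 1: both true differences zero.** Let ρ be the correlation between the estimated saving and the estimated QOL gain. So ρ = 0.7 means −0.7 between the cost and QOL differences. The article gives no value, and 0 to 0.7 is an assumed range. For bivariate normal estimates,

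P(cheaper and better) = 1/4 + arcsin(ρ)/(2π)

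| ρ | arcsin(ρ)/(2π) | P |
|---|---|---|
| 0 | 0 | 25.0% |
| 0.3 | 0.048 | 29.8% |
| 0.5 | 0.083 | 33.3% |
| 0.7 | 0.123 | 37.3% |

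Neither sample size nor SD enters. A simulation with skewed costs (lognormal, log-SD 0.8, 39 per arm, ρ applied to log cost) gave 25.1%, 29.3%, 32.1% and 35.0%, so skewness changes little.

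**Step 2: a programme with no effect.** The rule counts the programme's own cost, so the true net cost difference is then that cost, not zero. Let d be the programme cost divided by the standard error of the net cost difference. Then P = Φ₂(−d, 0; ρ), the bivariate normal distribution function. At ρ = 0 this is ½Φ(−d).

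| d | ρ = 0 | ρ = 0.3 | ρ = 0.5 | ρ = 0.7 |
|---|---|---|---|---|
| 0.13 | 22.4% | 27.2% | 30.7% | 34.6% |
| 0.25 | 20.1% | 24.8% | 28.1% | 31.9% |
| 0.5 | 15.4% | 19.7% | 22.7% | 26.0% |
| 1 | 7.9% | 10.8% | 12.7% | 14.5% |

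To place d, a cost SD and a programme cost must be assumed. For scale, the Background says: "The median cost of hospitalisation post oesophagectomy is $31,375 (€26,368), however this increases by a further $20,777 (€17,461", the further amount being for serious complications. Taking EUR 17,461 as an SD (an assumption; the article reports it as a cost increment), SE = 17,461 × √(2/39) = EUR 3,954. An assumed programme cost of EUR 500–2,000 is then 500/3,954 = 0.13 to 2,000/3,954 = 0.51 SE. The table rows for 0.13 and 0.5 give about 15–35%.

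The SD matters. EUR 2,000 is 0.88 SE at an SD of EUR 10,000 (SE 2,265) and 0.25 SE at EUR 35,000 (SE 7,926).

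**Step 3: the unnamed outcome.** With no QOL effect, P(costlier and worse) = ½ − Φ(−d) + P(cheaper and better).

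- d = 0: the same 25–37% as in Step 1.
- d = 0.5: 0.5 − 0.309 + 0.154 = 35% at ρ = 0, and 0.5 − 0.309 + 0.260 = 45% at ρ = 0.7.

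So the outcome that the rule does not name is at least as likely by chance as the one it does.

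**Step 4: what linking tests to the rule would do.** With zero true net differences:

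- Requiring both differences to be significant at two-sided 5% in favour of the programme gives 0.06% (ρ = 0) to 0.83% (ρ = 0.7).
- Requiring significance for net cost only, with QOL merely in the right direction, gives 1.3% to 2.5%.

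The article specifies neither. The comparison shows how much depends on the missing link.

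**The case against.** The best defence is that the sentence only gives the textbook definition of dominance and says when a ratio makes sense. It never mentions point estimates, QOL differences are to be analysed, and hospital-stay costs are to be tested. A fuller economic plan may hold the methods, and a condensed article need not list a bootstrap or an acceptability curve.

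Much of this stands. Reading the rule on point estimates is an inference, though the natural one. It would be wrong to say that the article ignores sampling error, because it plans cost tests. The absence of named economic methods is not in itself a fault.

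The defence does not remove the point. The planned tests concern hospital stays, whereas the rule uses cost including the programme. Nothing ties the tests to the conclusion, and no statement covers cost and QOL together. An article that prints both condition and conclusion has fixed the rule, so this is more than a detail left for later.

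The aim is secondary, and the primary analysis of VO2peak is unaffected.

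**Conclusion.** The point holds in a limited form. As printed, the rule can yield a claim of dominance with no joint uncertainty attached. On point estimates, its chance rate is 25% with zero true net differences and independent estimates, and 37% at an assumed correlation of −0.7.

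A reader might infer that a programme with no effect would be called dominant in 25–37% of trials. The article does not support that: programme cost is inside the rule, so an ineffective programme is truly costlier and the rate drops. It is about 15–35% under the assumed EUR 500–2,000 and SD of EUR 17,461, and 8–15% if the programme costs one standard error. Programme cost, cost SD and correlation are all assumptions. Most of these rates are still high for so strong a claim.

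A reader might also infer that the plan promises a meaningless ratio when the programme is costlier and worse. It does not. The fallback sentence speaks of the cost of an improvement in QOL, and in that case there is none. The outcome is left unaddressed; it is not assigned a wrong ratio.

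**What to change.** Replace the rule with a joint analysis:

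- Resample patients within arm, drawing total cost (hospital plus programme) and one named EQ-5D-5L utility measure together, for example utility at 3 months.
- Report both mean differences with bootstrap intervals and the share of resamples in each of the four quadrants.
- Report net monetary benefit over a stated threshold range. With a single-time utility, the threshold is per unit of that measure, not per QALY.
- Use dominant or dominated only with its bootstrap probability, and report no ratio in those two quadrants.
- Do not claim baseline-adjusted QALYs. No baseline EQ-5D-5L is scheduled, so they cannot be built from the planned data.

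This needs no extra patients or visits. The cost is a little more analysis work and a headline that is a probability instead of a flat verdict.
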